# Exploring the feasibility and acceptability of couple-based psychosexual support following prostate cancer surgery: study protocol for a pilot randomised controlled trial

**DOI:** 10.1186/1745-6215-15-183

**Published:** 2014-05-24

**Keywords:** Adjustment, Communication, Counselling, Couple, Functioning, Intervention, Prostate cancer, Psychological, Quality of life, Relationship, Sexual

## Abstract

**Background:**

Men who undergo surgery for prostate cancer frequently experience significant side-effects including urinary and sexual dysfunction. These difficulties can lead to anxiety, depression and reduced quality of life. Many partners also experience psychological distress. An additional impact can be on the couple relationship, with changes to intimacy, and unmet psychosexual supportive needs in relation to sexual recovery and rehabilitation. The aim of this exploratory randomised controlled trial pilot study is to determine the feasibility and acceptability of a novel family-relational-psychosexual intervention to support intimacy and reduce distress among couples following prostate cancer surgery and to estimate the efficacy of this intervention.

**Methods/Design:**

The intervention will comprise six sessions of psychosexual and relationship support delivered by experienced couple-support practitioners. Specialist training in delivering the intervention will be provided to practitioners and they will be guided by a detailed treatment manual based on systemic principles. Sixty-eight couples will be randomised to receive either the intervention or standard care (comprising usual follow-up hospital appointments). A pre-test, post-test design will be used to test the feasibility of the intervention (baseline, end of intervention and six-month follow-up) and its acceptability to couples and healthcare professionals (qualitative interviews). Both individual and relational outcome measures will assess sexual functioning, anxiety and depression, couple relationship, use of health services and erectile dysfunction medication/technologies. An economic analysis will estimate population costs of the intervention, compared to usual care, using simple modelling to evaluate the affordability of the intervention.

**Discussion:**

Given the increasing incidence and survival of post-operative men with prostate cancer, it is timely and appropriate to determine the feasibility of a definitive trial through a pilot randomised controlled trial of a family-relational-psychosexual intervention for couples. The study will provide evidence about the components of a couple-based intervention, its acceptability to patients and healthcare professionals, and its influence on sexual and relational functioning. Data from this study will be used to calculate sample sizes required for any definitive trial.

**Trial registration:**

ClinicalTrials.gov Identifier: NCT01842438.

Registration date: 24 April 2013; Randomisation of first patient: 13 May 2013

## Background

Surgery is a major treatment modality for prostate cancer [1] and has been hypothesised to reduce mortality more than other treatments for localised prostate cancer [2]. However, the risks of surgery are known to include erectile dysfunction [3] even when nerve-sparing approaches are used [4]. Long-lasting sexual and urinary difficulties are the most common and troubling side-effects following radical prostatectomy [5] alongside loss of libido, ejaculatory dysfunction, orgasmic dysfunction and penile shortening [6]. Even at 24 months post-operatively, most men have not returned to their baseline measure of sexual function prior to surgery [7]. These side-effects can be distressing for men and their partners due to the impact on psychological well-being and couple intimacy [8-11].

Many men affected by prostate cancer and erectile dysfunction experience symptoms of anxiety and depression [12,13], with reduced quality of life directly associated with urinary and sexual body-image changes that occur after surgery [14]. Partners of these men also experience considerable psychological distress [9,15-17], with anxiety and depression often reported at higher levels for partners than for patients [18,19]. The difficulties experienced after surgery can also impact on the couple relationship itself; for instance, erectile dysfunction is associated with reduced wellbeing [20,21] and lower levels of dyadic adjustment in the first year after surgery [22].

Prostate cancer has been described as a ‘relationship disease’ [23] and it has been established that couples affected by prostate cancer often have significant unmet psychosexual supportive care needs around sexual recovery and rehabilitation [24,25]. With such evidence of the impact of sexual dysfunction on relationships, there has been increasing interest in the development of couple-based psychosocial interventions that aim to improve wellbeing and relationship quality. Couple-based interventions have been effective in reducing psychological distress [26] and facilitating healthy communication [27,28]. Sexual rehabilitation therapy has been particularly helpful in increasing use of erectile dysfunction medications [29] and re-establishing a sexual relationship [30,31].

Evidence therefore exists to support the efficacy of couple-based interventions for reducing psychological distress, enhancing couple communication and improving relationship functioning among couples affected by cancer [32]. Interventions for couples affected by prostate cancer have targeted sexual functioning [31], relationship functioning [33], or combined both aspects [19,28,29,34,35]. Reviewed systematically, the overall effectiveness of such interventions remains inconclusive [36], although manualised face-to-face interventions that address the connection between sexual difficulties and relationship variables have shown improvements in sexual functioning, including erectile function. Chisholm *et al*. [36] conclude that the evidence remains weak due to methodological limitations, such as small sample sizes and ineffective outcome measures, while longer-term gains in functioning have been limited.

Of particular note, interventions have not been successful in improving both relationship and sexual functioning [36]. Consequently, it would be beneficial to devise an intervention framework that has a lasting impact on sexual *and* emotional aspects of the couple relationship. Studies suggest that understanding family-of-origin relationships may be important in supporting sexual functioning in marriage [37], and that to address sexual issues it is critical to support the relationship more generally [38]. Consequently, an approach which is family-relational and psychosexual combines key elements of a potentially fruitful intervention.

The current study offers a family-relational-psychosexual approach to supporting the couple, by combining family systems principles with elements of sex therapy. Combining these approaches enables the intervention to address broader relational issues that impact specific problems around sex and intimacy. The intervention therefore has the potential for long-term benefits to participants, as the wider context of prostate cancer and couple dynamics are a focus. It will develop a new way of supporting couples that combines family systems principles with elements of sex therapy to enhance intimacy and reduce distress. A family systems approach is based on an understanding that the family/relational context influences couple dynamics, which consequently impact on relational and psychosexual outcomes. The treatment model adopts a comprehensive approach to couple support, addressing communication and relationships within the family context, to address broader relational issues in which specific problems around sex and intimacy will be located.

### Aims

The primary aim of the study is to determine whether a family-relational-psychosexual intervention is feasible and acceptable for couples affected by prostate cancer in the context of one care-delivery setting. Subsidiary to this, the study aims to understand what processes of randomisation are plausible for a larger trial, determine a sample-size calculation for a definitive trial, and estimate the efficacy of the intervention to increase sexual and relationship functioning.

### Objectives

1. Design a family-relational-psychosexual treatment for delivering a couple-based intervention.

2. Determine the acceptability and feasibility of the intervention to patients, partners and healthcare professionals in the context of one care-delivery setting.

3. Determine sample size, recruitment and randomisation processes for a definitive trial.

4. Establish long-term cost implications to be addressed in a definitive trial.

## Methods

### Design

This study has been designed to develop and assess the feasibility of a couple-based intervention following prostate cancer surgery. The design encompasses phases i/ii of the Medical Research Council (MRC) complex intervention framework [39,40]. It embeds a two-arm pilot randomised controlled trial (RCT) followed by qualitative interviews assessing acceptability and feasibility of the intervention.

A pre-test, post-test design is being used to test the feasibility of the intervention (baseline, end of intervention and six-month follow-up). The study is underpinned by Realistic Evaluation methodology, which acknowledges the complexity of interventions and the contexts in which they are delivered and assessed [41]. This methodology ensures that data is gathered from a range of relevant stakeholders to identify facilitators and barriers to delivery and uptake. The aim is also to produce findings that will be of relevance in routine clinical practice.

### Setting and participants

Patients with prostate cancer and their partners are being recruited from a single site in one National Health Service (NHS) board: an outpatient surgical urology clinic at the Western General Hospital, Edinburgh (NHS Lothian), UK. The recruiting clinic sees patients from a wide catchment area covering four Health Boards in Scotland: the Borders; Dumfries and Galloway; Fife; the Lothians. Recruitment will take place over one year.

#### Eligibility

Eligible patients are all men who: (1) are >11 weeks post-operative for localised prostate cancer (to recruit men who have recovered from the immediate effects of surgery and who have consequently started to regain some functioning); (2) have received surgery in the previous two years (since long-term adaptation will have commenced in patients who have had surgery beyond this timeframe); (3) have a partner (in an established same-sex or different-sex relationship); (4) score ≤60 (the clinical threshold for potency [42]) on the sexual function domain of the Expanded Prostate Cancer Index Composite (EPIC).

Patients are excluded from the study if: (1) they have a prognosis of ≤1 year (most men who have had recent surgery will have a good prognosis, so it is unlikely that many men will be excluded by this criteria); (2) they reside in Dumfries and Galloway (to prevent excess burden travelling to the intervention site); (3) they cannot provide informed consent; (4) they are unable to communicate in English (this is a pilot trial, and if we move to a full-scale trial in future we would seek to include interpreters/translators).

#### Sample size calculation

The trial aims to recruit 68 men and partners at routine follow-up after surgery, with 30% over-recruitment to enable adjustment for loss to follow-up [43]. A sample size of 68 couples was calculated using G-Power [44] based on having 90% power to detect a small-to-medium effect size *f* of 0.20 on the primary outcome (using repeated measures analysis of variance (ANOVA) and testing the within-between group interaction in this two-group design with two points of measurement (end of intervention and six-month follow-up) at an alpha level of 0.05). A small-to-medium effect on sexual function was selected based on previous intervention effects seen for couple interventions in the cancer literature [45].

Assuming a baseline mean of 33 and a standard deviation of 24 on the sexual function subscale of the EPIC [46], this study will have 90% power to detect a mean difference of 9.6 units at the 0.05 level. This will allow the study to estimate the efficacy of this intervention on the mean difference in overall sexual function (as measured by EPIC) between the intervention and control groups pre- and post-test. The standardised difference observed will be used to calculate the sample size required for a definitive trial to test the efficacy of this intervention. The anticipated effect size of *f* of 0.20 on the primary outcome is a crude estimate, as it is based on a pooled estimate of a heterogeneous selection of couple interventions for several types of cancer [45].

Based on surgical data from the locale (2009 to 2011) we estimate that there will be 500 patients who will be between 12 weeks and two years from surgery during the one-year recruitment period. The estimated recruitment rate from a prior study with a similar population and intervention design was 21% [33]. As some of the patient population will be excluded from the study based on the eligibility criteria above, we anticipate contacting approximately 420 patients to recruit 88 couples (taking account of 30% over-recruitment [43] to achieve a sample size of 68 couples completing the study).

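### The stated 90% power for a 9.6-unit EPIC difference is wrong: 68 couples at f = 0.20 give 90% power for a 19.2-unit difference in change, and about 37% for 9.6 units

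*Protocol article*

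**What the plan says.** All the inputs are in the protocol article, Methods, Sample size calculation.

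- The size and software: "A sample size of 68 couples was calculated using G-Power".
- The target: "90% power to detect a small-to-medium effect size" f of 0.20.
- The test: repeated-measures ANOVA, "testing the within-between group interaction in this two-group design with two points of measurement", "at an alpha level of 0.05".
- The scale: "Assuming a baseline mean of 33 and a standard deviation of 24 on the sexual function subscale of the EPIC".
- The restatement in EPIC units: "this study will have 90% power to detect a mean difference of 9.6 units at the 0.05 level".

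The same paragraph describes that difference as one between the two arms, from before to after the intervention. The section also plans to recruit 88 couples so that 68 complete. Allocation is 1:1 (Randomisation, allocation concealment and blinding), so 34 completers per arm. The correlation between the two measurements is not given.

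**The concern.** The section presents f = 0.20 and 9.6 units as the same effect, each with 90% power. With SD 24, 9.6 units is 0.4 SD. A comparison of 34 against 34 does not normally have 90% power for 0.4 SD, so either the sample size or the conversion had to be wrong.

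The power statement bears on how the result will be read. The article says hypotheses are not formally tested. Yet Statistical analysis tests the interaction at 0.05, Phase 1 makes the offer of the intervention to controls depend on a significant benefit, and the Discussion says the study will settle whether the intervention works. A reader who believes the design had 90% power at 9.6 units would take a non-significant result as evidence against an effect of that size. The observed standardised difference is also to feed the sample size of the definitive trial, so confusing 0.4 SD with 0.8 SD could carry forward.

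**Working it through.** **Inputs.** N = 68 (34 per arm), k = 2 groups, m = 2 measurements, f = 0.20, alpha 0.05, SD 24, stated difference 9.6 units, all from the protocol. The correlation ρ is not stated and is inferred in step 1.

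**1. Reproduce the 68.** For the G-Power within-between interaction, λ = f² × N × m / (1 − ρ), with 1 and (N − k)(m − 1) = 66 degrees of freedom. With ρ = 0.5:

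λ = 0.04 × 68 × 2 / 0.5 = 10.88, power 0.9015.

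N = 66 gives 0.893, so 68 is the smallest even total. The smallest even N would be 76 at ρ = 0.45 and 62 at ρ = 0.55. The protocol's own 68 therefore points to ρ = 0.5.

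**2. Convert f to EPIC units.** In a 2×2 interaction each of the four cell means departs by f × SD = 0.20 × 24 = 4.8 units, with alternating signs. Each arm's change then differs from the average change by 2 × 4.8 = 9.6 units, in opposite directions. The difference in change between arms is:

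4 × 0.20 × 24 = 19.2 units = 0.8 SD.

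This step does not depend on ρ. The stated 9.6 is 2 × 0.20 × 24, the conversion for a two-group main effect. That effect has a different sample size: a between-group main effect at f = 0.20, with two measurements and ρ = 0.5, needs 200 couples for 90% power.

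**3. Cross-check on change scores.** SD of change = 24 × √(2(1 − 0.5)) = 24. SE of the difference = 24 × √(2/34) = 5.82.

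- 19.2 / 5.82 = 3.30, whose square is 10.88, the λ of step 1. Power 0.9015 (simulation 0.899).
- 9.6 / 5.82 = 1.649. Power 0.369 (simulation 0.372).

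**4. Power at 9.6 units under other analyses** (34 per arm, ρ = 0.5):

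| Analysis | Residual SD if SD = 24 | Power, SD 24 | Power, SD 15.5 |
|---|---|---|---|
| Difference in change, or one unadjusted follow-up | 24.0 | 37% | 71% |
| ANCOVA, one follow-up | 24 × √(1 − 0.25) = 20.8 | 47% | 83% |
| ANCOVA, mean of both follow-ups | 24 × √(0.75 − 0.25) = 17.0 | 63% | 94% |

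The last column is a sensitivity case. Entry requires a score of 60 or less, and a normal distribution with mean 33 and SD 24 cut to 0–60 has an SD of about 15.5.

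**5. What would make 9.6 true.**

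- At N = 68 and SD 24, power for a 9.6-unit difference in change is 21% at ρ = 0, 28% at 0.3, 37% at 0.5, 55% at 0.7 and 73% at 0.8. It reaches 90% only at ρ = 0.875, where f = 0.20 would need about 20 couples. No single ρ makes both statements true.
- A single unadjusted follow-up comparison at 0.4 SD needs 133 completers per arm, about 266 in all.

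**6. Precision with 34 per arm, SD 24.** The 95% confidence interval half-width for one follow-up is 2.00 × 5.82 = ±11.6 units unadjusted, and ±10.1 with baseline adjustment at ρ = 0.5 (SE × √0.75).

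**The case against.** The strongest reply is that the error does no damage to the design. N was set from f, not from 9.6, so correcting the sentence changes no sample size. The primary aim is feasibility and acceptability, the article says it is not formally testing hypotheses, and it calls f = 0.20 a crude estimate. This lessens the consequence but does not make the stated power correct, and the article still relies on significance in the places noted above.

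The percentages depend on assumptions. The 37% needs ρ = 0.5 and SD 24, and higher correlation or a narrower SD raises it. At SD 15.5 and ρ = 0.7, even the difference in change reaches 90%. The SD of 15.5 is itself speculative: it assumes normality and carries an entry restriction over to follow-up, and cutting only at 60 gives 19.6. These points stand as limits on the exact figures. They do not rescue the sentence, which assumes SD 24 alongside an N that implies ρ = 0.5.

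It is also fair that f = 0.20 may be called small-to-medium on the f scale. The label misleads once it is attached to 9.6 units, because the difference in change actually powered for is 0.8 SD.

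Two readings do give 9.6 with 90% power. One is a pooled pre-post change in all 68 couples (90.2%), but that is not a comparison between arms. The other is a gap of +9.6 at one time and −9.6 at the other, which is still a 19.2-unit difference in change.

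Finally, the two time points named for the test are both after baseline, "two points of measurement (end of intervention and six-month follow-up) at an alpha level of 0.05", while the next paragraph speaks of change from before to after. Any restatement should say which change it means.

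**Conclusion.** The concern holds. The sample size is right for f = 0.20 under the named test, but its translation into EPIC units is too small by a factor of two. The 90% belongs to a 19.2-unit (0.8 SD) difference in change. At 9.6 units the planned test has about 37% power, so a true effect of that size would more often be missed than found.

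The factor of two follows from the 2×2 structure alone. The 90% and 37% rest on SD 24, 34 completers per arm and the correlation of 0.5 that the protocol's N implies. With the same SD and correlation, no analysis considered exceeds 63% at 9.6 units. A narrower SD in the selected population could raise these figures, and at SD 15.5 and correlation 0.5 only ANCOVA on the mean of both follow-ups passes 90%. This needs correcting because the article claims a power that the design, on its own assumptions, does not have.

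**What to change.** Replace the power sentence in Sample size calculation with wording such as:

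> With 68 completing couples, SD 24 and a correlation of 0.5 between measurements, the interaction test has 90% power for a between-arm difference in change of 19.2 EPIC units (0.8 SD). For a difference of 9.6 units, power is about 37% for that test and up to about 63% with ANCOVA on the mean of both follow-ups.

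Also:

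- State the correlation used and which two time points define the change.
- Note that an SD of 24 may not hold in men selected at a score of 60 or less.
- Justify the 68 on precision: an expected 95% confidence interval half-width of about ±11.6 units for one unadjusted follow-up, or ±10.1 with baseline adjustment at correlation 0.5.

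Keep the sample size. The cost is a text change and a less favourable stated power, with no extra couples or procedures.

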### Phase 2: determining the parameters for a definitive trial

#### Patient recruitment

Eligible patients will be identified from the urology surgical lists at the Western General Hospital, Edinburgh, UK. The research nurse at the site will apply eligibility criteria before patients are invited to complete the EPIC questionnaire. Patients will be invited to complete the questionnaire via two routes: either on-site at their post-operative follow-up appointment at the outpatient surgical urology follow-up clinic; or by postal invitation from the clinical team.

The recruiting site will complete logs to report recruitment rates at baseline and any attrition following randomisation. Additionally, attendance at the couple support sessions will be logged to assess attrition rates at each stage of the intervention. The recruitment rate for a larger definitive trial will be calculated from the time taken for 68 couples to complete the study.

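### The definitive trial's recruitment rate is to come from one pooled, time-based figure, although nearly two thirds of the pilot's pool may be a backlog already eligible on opening day

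*Protocol article*

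**What the plan says.** The Eligibility section admits men who "are >11 weeks post-operative for localised prostate cancer" and who "have received surgery in the previous two years". Under Setting and participants: "Recruitment will take place over one year". The Sample size calculation section uses local surgical data from 2009 to 2011 to size the pool: "we estimate that there will be 500 patients who will be between 12 weeks and two years from surgery during the one-year recruitment period". It does not give the annual number of operations. It expects to contact about 420 men at 21% uptake to recruit 88 couples, which is 68 plus 30%.

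The Patient recruitment section fixes how the result is carried forward: "The recruitment rate for a larger definitive trial will be calculated from the time taken for 68 couples to complete the study". The third objective is to "Determine sample size, recruitment and randomisation processes for a definitive trial", so this rate is one of the pilot's intended outputs.

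**The concern.** Eligibility looks back almost two years, but recruitment lasts one year. The men eligible at some time in that year are of two kinds: those already in the window when the trial opens, and those who reach the lower limit during the year. The first group is a stock, which a site can invite only once. The second is a flow, which continues as long as surgery continues. A single rate per unit of time treats the stock as if it were flow.

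The pilot could meet its target exactly and still give a rate that the same site could not repeat in the following year. A definitive trial planned on it could have too few sites or too short an accrual period. Counting time correctly, as recruits per recruitment month, would not remove the problem.

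**Working it through.** **Inputs from the protocol article.** Pool 500; window from 12 weeks to two years; recruitment 1 year; 420 contacted (420/500 = 84%); uptake 21%; 88 couples recruited, 68 completing. **Assumptions:** constant surgical volume *s* per year, and equal uptake in backlog and new men.

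**The plan's own figure.** 0.21 × 420 = 88.2 and 68 × 1.30 = 88.4. Both reproduce 88.

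**Window.** w = 2 − 12/52 = 1.77 years (1.79 if the lower limit is 11 weeks, as in the Eligibility section).

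**Literal reading: 500 men eligible at some time in the year.**
- Men eligible in the year = s(w + 1), so s = 500/2.77 ≈ 181 a year.
- Already in the window at opening: 500 × 1.77/2.77 ≈ 319, or 64%.
- Couples from new entrants: 181 × 0.84 × 0.21 ≈ 32. From the backlog: 319 × 0.84 × 0.21 ≈ 56. Together 88.
- If 84% is not an eligibility fraction and is left out: 181 × 0.21 ≈ 38 couples a year from new entrants.
- Pilot year against sustained flow: 500/s = 2.77 (2.79 with 11 weeks). With 38 a year it is 88/38 = 2.3.

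**A site that opens with its own backlog.** Over T years it recruits 56 + 32T couples. The pooled rate would predict 88T.

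| Years of accrual | Pooled rate predicts | Backlog plus flow | Ratio |
|---|---|---|---|
| 1 | 88 | 88 | 1.0 |
| 2 | 176 | 120 | 1.47 |
| 3 | 264 | 152 | 1.74 |

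**The rate as the Patient recruitment section defines it.** Six sessions every two to three weeks take about 10 to 18 weeks, and follow-up adds six months. If recruitment fills the year, 68 couples have finished after about 1.7 to 1.85 years, which is 37 to 40 a year. Sustained completers from new entrants are 32 × 68/88 ≈ 25 a year. The ratio is 37/25 to 40/25, about 1.5 to 1.6.

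**Alternative reading: 500 men eligible at one moment.**
- s = 500/1.77 ≈ 282 a year, and new entrants give 282 × 0.84 × 0.21 ≈ 50 couples a year.
- With the pilot limited to 500 men, the ratio for a site with its own backlog, w/[(w + T)/T], is 0.64, 0.94 and 1.11 for T = 1, 2 and 3.
- For the rate as defined, sustained completers are 50 × 68/88 ≈ 39 a year against 37 to 40, a ratio of about 1.0.
- 88/50 is about 1.8. However, the pool over the year would then be about 500 + 282 = 782 men, so 88 would be a target and not the yield of the pool.

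**The case against.** A reader might infer that the pilot's rate overstates what any definitive trial can sustain by 1.8 to 2.8 times. The documents do not support that. The upper figure is a limit that holds only once the backlog is gone. New sites using the same window would open with a backlog of their own, and the article gives neither the number of sites nor the duration of a definitive trial. The lower figure needs 500 to be a count at one moment, which is not the literal wording, and it compares a recruitment target with a flow. Neither figure applies directly to the rate the protocol defines, because intervention and follow-up time dilute it. This is a separate defect that partly cancels the backlog effect.

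Three further points stand in part. The Discussion refers to rising incidence; if surgical volume rises too, new entrants are a larger share and every factor falls. Men are approached mainly at follow-up clinics, with post used on busy days, so some backlog men may pass two years before being approached, and no opening-day mailing is described. The 21% uptake per man contacted is not inflated by the size of the pool.

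It can also be said that tabulation by surgery date is a detail an article leaves to the full protocol. That would be fair if the article were silent. Instead it states the rule for the projection, and that rule has no place for a backlog.

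**Conclusion.** The concern holds in a bounded form. On the literal reading and with steady volume, about 64% of the pool is backlog, and new entrants alone supply about 32 couples a year (38 without the 84%) against 88. The one-year recruitment rate may overstate sustained single-site accrual by up to about 2.8 times. For sites with their own backlog, the factor is about 1.0 at one year, 1.5 at two and 1.7 at three. The rate as the protocol defines it overstates sustained completers by about 1.5 to 1.6. If 500 is a count at one moment, overstatement over one to three years is small or absent.

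The size thus depends on the annual surgical volume, the meaning of 500 and the design of the definitive trial, none of which the article settles. What does not depend on them is that no single pooled rate can be right for every accrual period when stock and flow are mixed.

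**What to change.** In the recruitment logs, classify each invited man by date of surgery as already in the window when the trial opened or newly eligible during the recruitment year. Report invitations, EPIC eligibility and recruitment for each group. Replace the rule based on the time for 68 couples to finish with a projection that has two parts: a one-off backlog per site, and the newly eligible flow per month, each multiplied by uptake per eligible man. State whether 500 is a count over the year or at one moment, and give the annual number of operations behind it.

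The cost is one extra tabulation and a sentence or two in the protocol. Patients are already identified from the surgical lists and recruitment logs are already planned. Eligibility, treatment and sample size do not change. The drawback is that the recruitment outlook may look less favourable.

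### The abstract says 68 couples will be randomised, but the body makes 68 the completers and 88 the number randomised; the 30% over-recruitment covers a loss of at most about 23%

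*Protocol article*

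**What the plan says.** The abstract of the protocol article, under Methods/Design, gives one figure: "Sixty-eight couples will be randomised to receive either the intervention or standard care".

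The Sample size calculation section opens with "The trial aims to recruit 68 men and partners at routine follow-up after surgery, with 30% over-recruitment to enable adjustment for loss to follow-up". It derives 68 from 90% power at effect size f = 0.20, for the within-between interaction with two groups and two measurements at alpha 0.05. Its last paragraph then plans, from about 420 patients contacted, to "recruit 88 couples (taking account of 30% over-recruitment [43] to achieve a sample size of 68 couples completing the study".

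The Patient recruitment section also uses 68 as a number completing: the recruitment rate for a later trial is to come from the time it takes 68 couples to finish the study.

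The section on randomisation, allocation concealment and blinding places randomisation after consent and return of baseline data, with 1:1 allocation. No section shown gives an expected loss-to-follow-up rate. The 30% appears only as a percentage of over-recruitment.

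**The concern.** The figure 68 has two roles that cannot both hold. In the abstract it is the number entering the randomised comparison; in the body it is the number left at the end. The difference is 20 couples.

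The power statement belongs to the second role. If 68 were the number randomised, the stated 90% would be reached only with no loss at all, although the same article plans for loss.

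A second point belongs in the same correction. The 30% is tied to loss to follow-up but no loss rate is given, so a reader cannot tell what retention the plan assumes. That matters in a pilot meant to measure recruitment and retention and to inform the size of a definitive trial.

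**Working it through.** **Inputs from the article.** 68 couples randomised (abstract). From Sample size calculation: 68 couples completing, 88 recruited, 30% over-recruitment, about 420 patients contacted, 21% recruitment rate, f = 0.20, 90% power, alpha 0.05, two groups and two measurements.

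**Input that is an assumption.** The correlation ρ between the two measurements is not stated. I use 0.5 and show 0.3 and 0.7 beside it.

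**1. Reproduce the plan's figures.**
- Over-recruitment: 68 × 1.30 = 88.4, matching 88.
- Contacts: 420 × 0.21 = 88.2, matching 88.
- Base sample size: noncentral F with λ = f² × N × m / (1 − ρ), on 1 and N − 2 degrees of freedom. For N = 68, m = 2, ρ = 0.5: λ = 0.04 × 68 × 2 / 0.5 = 10.88, power 0.902. N = 68 is the smallest even N that reaches 0.90.

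All three agree with the article, the last under ρ = 0.5.

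**2. Which number is randomised?** One way to reconcile the figures would be that 88 are recruited and 68 of them randomised. The article rules this out. Couples are randomised once consent and baseline data are in, and the extra couples are there to absorb loss to follow-up, which comes after randomisation. The 88 recruited are therefore the couples randomised.

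**3. What loss does 88 allow?** (88 − 68)/88 = 20/88 = 22.7%.

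**4. What if 68 were randomised?**
- At the loss that 88 is able to absorb: 68 × 68/88 = 52.5, about 53 completers.
- At 30% loss: 68 × 0.70 = 47.6, about 48 completers.

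**5. What if 88 are randomised and 30% are lost?** 88 × 0.70 = 61.6, about 62 completers.

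**6. Power at f = 0.20, alpha 0.05.**

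| Completers | Scenario | ρ = 0.3 | ρ = 0.5 | ρ = 0.7 |
|---|---|---|---|---|
| 68 | 88 randomised, 22.7% lost | 0.78 | 0.90 | 0.99 |
| 62 | 88 randomised, 30% lost | 0.75 | 0.87 | 0.98 |
| 53 | 68 randomised, about 23% lost | 0.68 | 0.81 | 0.96 |
| 48 | 68 randomised, 30% lost | 0.63 | 0.77 | 0.94 |

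Of the three values, only ρ = 0.5 gives 90% at N = 68. At ρ = 0.5, 52 completers give 0.807 and 53 give 0.815, so 0.81 serves for either rounding.

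**The case against.** A reader might infer that 88 is an arithmetic error: that 30% loss was planned, and 68 was multiplied by 1.30 when it should have been divided by 0.70. The document does not support that. Its words are "taking account of 30% over-recruitment", it never states a 30% loss rate, and 68 plus 30% is 88. The source cited for the 30% is not at hand, so what was meant cannot be settled. The division (68/0.70 = 97.1, so 98 couples, or 98/0.21 = about 467 contacts against the 420 planned) applies only if 30% was the expected loss and 68 completers had to be held. What stands is narrower: 30% over-recruitment covers less than 30% loss, and the article should say how much.

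It can also be said that the body agrees with itself. The opening sentence of the sample size section gives 68 together with its over-recruitment, and the closing sentence gives 88 for 68 completing. That is fair: the opening is loosely worded, and only the abstract conflicts.

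A reader might further infer that enrolment will stop at 68. No such rule is stated; recruitment is set to run for one year. The 48 and 53 completer scenarios show what the abstract would mean if taken literally. They do not forecast what will happen.

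Lastly, this is a feasibility pilot that says it is not formally testing hypotheses, so a modest loss of power is not decisive. That limits the seriousness of the point. It does not remove the conflict, because the article states the power and builds its sample size on it.

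**Conclusion.** The conflict is real and follows from the text alone: the abstract's 68 randomised cannot stand beside the body's 88 recruited and 68 completing, and the order of consent, baseline and randomisation makes 88 the number randomised. Read literally, the abstract is 20 couples short, and at about 23% loss it would leave about 53 completers with power about 0.81 in place of 0.90.

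The 88 is not shown to be miscalculated. It tolerates a loss of at most about 23%. If the sponsor does expect 30%, about 62 couples would complete, with power about 0.87. The power figures depend on ρ = 0.5, which is assumed; the completer counts and the 22.7% do not. The point deserves correction because the sample size should be stated once and correctly, but for a pilot it is a moderate matter of clarity and does not threaten the design.

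**What to change.** 1. State 88 couples randomised and 68 completing wherever the sample size appears. Correct the abstract, and reword the opening of the sample size section so that 68 is plainly the number completing.
2. State the expected loss to follow-up. If it is about 23% or less, say that recruiting 88 (68 × 1.30) covers a loss of up to 20/88.
3. If 30% loss is what is expected, keep 88 and restate the expected completers as about 62, with the lower power (about 0.87 at ρ = 0.5). Give the correlation used in the power calculation so that the figure can be checked.

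The cost is wording only: no extra couples, contacts or design change, and at most a slightly less favourable stated loss allowance, completer number or power.
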